### Statistical analysis

All data will be coded and collected in a secure web browser clinical data management platform (ALEA Clinical). All analyses will be performed using the latest version of IBM SPSS Statistics and R [39], will be two sided and considered significant if p < 0.05. Multivariate Imputation by Chained Equations (MICE) will be used to handle missing data where possible. Descriptive statistics will be generated to summarize patients’ demographics and medical disease characteristics by study site and by intervention (i.e. without vs. with use of CDSS-OPTIMED).

As assessed with an intention-to-treat approach, we will compare patients’ quality of life between patients who were enrolled in the study prior to the use of the CDSS-OPTIMED and patients who were enrolled after implementation of the CDSS-OPTIMED. In a multilevel multivariable regression analysis, with quality of life as the dependent variable, we will take into account the stepped wedge cluster randomized design of the study, and potential baseline differences (including baseline quality of life) between patients in the intervention and control group.

The following secondary analyses will be performed. Firstly, symptom scores at day 7, 14, 21, 28 and then every 28 days until death after baseline assessment will be compared between patients who were enrolled in the study prior to the use of the CDSS-OPTIMED and patients who were enrolled after implementation of the CDSS-OPTIMED, using a multilevel multivariable regression analysis and an intention to treat approach, similar to the analysis of the primary outcome. Secondly, similar analyses will be performed to compare patients’ quality of life at day 7, 21, 28, and then every 28 days until death. Thirdly, cox regression analysis will be used to compare overall survival. Fourthly, the use of medication two weeks after baseline assessment and used medications and interventions from baseline until death will be compared between the respective groups of patients using parametric or non-parametric methods, where appropriate. Furthermore, a cost-effectiveness analysis, using a within-trial incremental cost-effectiveness analysis, will be performed to compare the control group (‘care as usual’) with the intervention group (the use of CDSS-OPTIMED).

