### Study design

The AMUSE study is a multicentre stepped-wedge cluster randomized controlled trial that evaluates the effect of weekly personalized medication recommendations provided by CDSS-OPTIMED. The stepped-wedge design will involve random and sequential crossover of clusters, the different study sites being the clusters, from the control to the intervention group, until all clusters are exposed. A schematic illustration of the study method is highlighted in Fig. 1. All clusters will start as control sites, where care is provided as usual. Every twelve weeks, one study site will crossover from control to intervention group. Since seven study sites will be included and will switch from control to intervention with one site per step, seven steps are included, resulting in eight observation periods in 96 weeks. Sites will crossover from control to the intervention group in a random order. Within two weeks before and ultimately two weeks after starting the crossover, physicians will be trained to use CDSS-OPTIMED. Within these four weeks of training there will be a period of non-inclusion. In the intervention group, the attending physicians will receive weekly personalized medication recommendations.

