### Sample size calculation

The primary endpoint on which the sample size calculation is based is patients’ quality of life two weeks after baseline assessment as measured by the EORTC QLQ-C15 PAL questionnaire, quality of life question. The calculation needs to take into account both the clustered nature as well as the stepped wedge design of the study. Since 7 clusters will be included and will switch from control to intervention one-by-one, 7 steps will be present in the design, resulting in 8 observation periods. The intra-cluster correlation (ICC) is assumed to be 0.05. Based on unpublished own research, it is assumed that the standard deviation of quality of life measured by the EORTC QLQ-C15-PAL questionnaire is 23 (score will be rescaled to a scale from 0 to 100) and the difference to be detected should lie between 10 and 15 points. The desired power level is 80% and a two-sided alpha of 5% is used. Given expected numbers of available patients per cluster per month, the average number of patients that will be recruited per observation period per cluster will be 4.5. If the average number is 4, a total number of 224 patients will be included, whereas a total of 280 patients will be included when the average number is 5. Given these sample sizes, differences can be shown with 80% power if they are at least 13.03 points and 11.84 points, respectively [37, 38]. Since the average number of patients per cluster per observation period lies in between 4 and 5, it is expected that a total of 250 patients will be included and a clinically relevant effect can be shown.

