Lastly, another challenge of this study could be the methodological complexities of the stepped wedge cluster randomized controlled trial design. This is a novel study design that is increasingly being used in the evaluation of service innovations in healthcare organisations [38, 52]. We have chosen this study design because the CDSS-OPTIMED intervention cannot be implemented all at once but must be rolled out sequentially. However, the stepped wedge design has also some methodological complexities, including the possibility of within cluster contamination, and the possibility of time varying treatment effects [38]. Statistical analysis and simple size calculation will account for the confounding effect of time. In addition, the statistical analysis will take into account both the clustered nature as well as the stepped wedge design of the study. In developing this study, we have tried to avoid within-cluster contamination, because participating patients cannot be exposed to both the control group and the intervention group, and we have built transition periods into the design.

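### Medication use and survival are given methods not tied to the site and calendar-period adjustment that the symptom and quality-of-life analyses carry

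*Protocol article*

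**What the plan says.** In the Protocol article, Statistical analysis, the primary model for quality of life is a multilevel regression of which the authors write "we will take into account the stepped wedge cluster randomized design of the study". Four secondary comparisons follow. Symptom scores come first, "using a multilevel multivariable regression analysis and an intention to treat approach, similar to the analysis of the primary outcome". Quality of life at the other time points comes second and is to be analysed in a similar way. The third is survival: "Thirdly, cox regression analysis will be used to compare overall survival". The fourth is medication use at two weeks, and medications and interventions from baseline to death; these "will be compared between the respective groups of patients using parametric or non-parametric methods, where appropriate".

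The Discussion adds two general statements: "Statistical analysis and simple size calculation will account for the confounding effect of time", and "In addition, the statistical analysis will take into account both the clustered nature as well as the stepped wedge design of the study". Neither is limited to particular outcomes.

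On the layout, Study design says "Every twelve weeks, one study site will crossover from control to intervention group", and Sample size calculation says "7 steps will be present in the design, resulting in 8 observation periods".

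**The concern.** In a stepped wedge the two groups differ by construction in calendar time, and they differ in site mix. A comparison that ignores period picks up any secular change as a treatment effect. One that ignores site understates the variance. The Statistical analysis section carries the design-based model over to the first two secondary analyses and names other methods for the third and fourth.

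Medication use is what the intervention acts on most directly, and survival bears on whether deprescribing is safe. The article applies p < 0.05 to all analyses, so both comparisons would be read as tests. A crude comparison could report a difference that is only early versus late enrolment, or hide a real one.

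**Working it through.** **Inputs.** From Study design and Sample size calculation: 7 sites, one crossing every 12 weeks, 8 periods, on average 4.5 patients per site-period, ICC 0.05 and SD 23 (both for quality of life), two-sided alpha 5%, power 80%. The article gives no ICC for medication use or survival and no secular trend, so ranges are used for these.

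**The plan's own figure.** The stepped-wedge design effect with k = 7 steps, one baseline and one follow-up measurement, and m patients per site-period is

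DE = [1 + ρ(7m + m − 1)] / [1 + ρ(3.5m + m − 1)] × 3(1 − ρ) / [2(7 − 1/7)].

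- m = 4: DE = (2.55/1.85) × 0.2078 = 0.2864. Detectable difference = (1.960 + 0.842) × 23 × √(4 × 0.2864 × 8/224) = 13.03.
- m = 5: DE = (2.95/2.075) × 0.2078 = 0.2954. Detectable difference = (1.960 + 0.842) × 23 × √(4 × 0.2954 × 8/280) = 11.84.

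Both stated values reproduce. They presuppose a model with site and period effects. No figure is stated for medication use or survival.

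**Time imbalance.** The i-th site to cross is control in periods 1 to i and intervention in periods i + 1 to 8. That makes 28 control and 28 intervention cells.

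- Control mean period: Σ i(i + 1)/2 ÷ 28 = 84/28 = 3.0.
- Intervention mean period: (7 × 36 − 84)/28 = 168/28 = 6.0.
- Gap: 3 periods, or 36 weeks. A linear drift of b per period shifts the crude difference by 3b, whatever the order of sites.

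The four-week non-inclusion window does not shrink the gap. If control enrolment at site i stops at week 12i − 2, the control mean is Σ(12i − 2)²/2 ÷ Σ(12i − 2) = 9,422/322 = 29.3 weeks. By symmetry the intervention mean is 96 − 29.3 = 66.7 weeks, so the gap is about 37.5 weeks.

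**Site imbalance.** The intervention share of a site's cells runs from 7/8 (87.5%) for the first to cross to 1/8 (12.5%) for the last. In the crude difference, site i's effect has weight (8 − i)/28 − i/28 = (8 − 2i)/28. The squares sum to 112/784 = 0.1429.

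**Type I error without drift.** With 4.5 × 28 = 126 patients per group, a pooled test uses the variance σ² × 2/126 = 0.01587σ². The true variance is 0.1429ρσ² + 0.01587(1 − ρ)σ². Their ratio is R = 9ρ + (1 − ρ) = 1 + 8ρ, and the type I error is 2[1 − Φ(1.96/√R)].

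- ρ = 0: R = 1.00, 5%.
- ρ = 0.05: R = 1.40, 9.8%.
- ρ = 0.10: R = 1.80, 14.4%.

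**Simulation under no effect** (2,000 trials per setting, Poisson mean 4.5 per cell). Drift is the total change over the 8 periods, in SD for the continuous outcome and in log hazard for survival. Survival is exponential with all deaths observed.

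| ICC | Drift | Pooled t-test | Unadjusted Cox | Linear model with site and period |
|---|---|---|---|---|
| 0 | 0 | 4.8% | 5.9% | 4.1% |
| 0.05 | 0 | 10.2% | 13.3% | 4.6% |
| 0.05 | 0.25 | 18.3% | 19.5% | 4.6% |
| 0.05 | 0.5 | 40.8% | 40.2% | 5.2% |
| 0.10 | 0 | 15.2% | 20.8% | 6.1% |

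Unequal site sizes gave similar results. A Cox model with site and period was not simulated.

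**The case against.** A reader might infer that the article prescribes unadjusted analyses of survival and medication use, and so contradicts its own Discussion. The text does not support that. It nowhere calls these analyses unadjusted or says that site or period is left out. Cox regression can hold period terms, site strata or a frailty, and a parametric method can be a mixed model. The two Discussion statements cover the statistical analysis as a whole. A condensed article also commonly leaves covariates of secondary models to the full protocol or analysis plan, which are not shown. For survival this objection largely stands, and what remains is a missing link.

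For medication use it stands less well. A choice between parametric and non-parametric methods for comparing groups is the usual description of a t-test or rank test, and these have no place for site or period. The section had just shown how to carry the design over, and here it named something else.

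A reader might also infer that site mix biases survival in a known direction. If hospice patients had twice the hazard, and sites were of equal size, the crude hazard ratio under no effect would be about 0.89 with the hospice crossing last and 1.11 with it first. But that hazard is assumed, and in the third to fifth positions the ratio is 0.95 to 1.04. Because step order is random, site mix adds variance and no systematic bias. The bias from calendar time does not depend on the order.

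**Conclusion.** The concern holds in a limited form. The Statistical analysis section assigns medication use to two-group comparisons that do not suit a stepped wedge. It assigns survival to Cox regression without tying it to the adjustment promised in the Discussion.

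The size is conditional on the analyses being run as worded. The 36-week gap and the bias of 3b follow from the layout with equal expected enrolment per site-period. The size of b is unknown. The type I error of about 10% requires an ICC of 0.05 for these outcomes, which is borrowed from quality of life; at ICC 0 without drift there is no inflation.

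Severity is moderate. The primary analysis and the symptom and quality-of-life comparisons are not touched.

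**What to change.** - **Medication use:** replace the two-group comparison with a mixed model, linear or count as the variable requires, with site and calendar period as in the primary analysis.
- **Survival:** state that the Cox model is stratified by site, or has a site frailty, and is adjusted for calendar period of enrolment.
- **Medication from baseline to death:** allow for unequal observation time, for example as a rate per day alive. The two-week comparison is already at a fixed time and needs only the model change.

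This is a change of wording, and site and enrolment date are already known for every patient. The cost is precision. For a continuous outcome with ICC 0.05 and 4.5 patients per site-period, DE = 0.2912. The adjusted standard error is then √(4 × 0.2912 × 8/252) = 0.192 SD, against √(2/126) = 0.126 SD from a pooled test. Intervals would be about 1.5 times as wide as those a pooled test would print, but the pooled intervals would be too narrow for this design.

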## Discussion

The AMUSE study is a multicentre stepped-wedge cluster randomized controlled trial that examines whether the use of CDSS-OPTIMED, a software program that gives weekly personalized medication recommendations to attending physicians of patients with a life expectancy of three months or less, improves patients’ quality of life.

This is the first study investigating whether carefully reviewing medication use of patients with a limited life expectancy, by means of weekly personalized medication recommendations, will increase patients’ quality of life. Until now, the exact consequences of carefully reviewing medication use in the last phase of life are lacking.

There is growing awareness that the use of medication in patients with a limited life expectancy needs careful consideration and that PIMs should be discontinued whenever possible [14, 18, 19]. To give physicians more guidance on medication deprescription in the last phase of life, different medication deprescribing tools and guidelines were developed for the geriatric population [29, 40, 41], and for patients with advanced cancer [7, 34, 42–44]. However, none of these tools or guidelines are aimed at the general population with a limited life expectancy. Improving medication deprescription in patients with a limited life expectancy requires an approach that is specifically designed and validated for this population. Recently, a Delphi study analysed the existing literature to develop recommendations on deprescribing medications for patients with a life expectancy of six months maximum. Our study integrated these recommendations into the software program CDSS-OPTIMED.

By using the validated software program CDSS-OPTIMED, medication reviews and therefore medication recommendations are provided in a standardized automatically way, which will result in more well-considered prescription [45]. In addition, the software program is expected to be user-friendly and is expected to save time compared to manual medication review, and will therefore improve medication review effectiveness [46]. Another advantage of using a validated software program is that the medication recommendations, based on the analysis of patient’s medication, will be given automatically on a weekly basis. Since limited awareness of proactively deprescribing medication among physicians is an important reason why medication is continued [20], we expect that recommendations given on a regular basis will create lasting awareness among physicians and provide them with continuous practical support for effective medication management.

This study has a multicentre design, to be conducted in seven different study sites across the Netherlands: one inpatient hospice facility, two general practices and four hospitals. By including patients with a limited life expectancy from multiple clinical sites and including patients with different main diagnoses and comorbidities, we expect that our study findings can ultimately be widely implemented.

We also expect to encounter several challenges in the AMUSE study. Firstly, the main challenge will be recruiting patients with a limited life expectancy for research. Patients with a limited life expectancy are considered vulnerable and fragile due to their illness, and may experience fluctuating symptoms and levels of suffering across their disease trajectory [47]. In addition, relatives or healthcare professionals may be hesitant to grant researchers access to incurably ill patients, due to concerns about burdening or distressing them, a phenomenon referred to as ‘gatekeeping’ [48]. However, multiple studies have shown that patients who are receiving palliative care are willing to participate in medical research and may benefit from their participation [47, 49, 50]. Nevertheless, it is important to reduce the burden during the study for patients with a limited life expectancy [51]. To reduce such burden, we will use short questionnaires for patients to complete, and we will give patients the opportunity to choose how the questionnaires will be completed (digitally or on paper). To minimize problems relating to the number of included patients, we have involved multiple clinical sites and planned for modest numbers of participants per site.

Secondly, another challenge of the study could be the high drop-out of patients as a result of patient’s death, gatekeeping [48], or patient’s deteriorating health condition [47]. Consequently, patients may not reach our primary endpoint two weeks after the baseline assessment and may not be able to complete the follow-up period. To minimize the risk of drop-out, we will maintain frequent contact with the patient during the study if the patient has given permission for this. In addition, we strive to minimize the drop-out by reducing the burden for patients by using only short questionnaires.

Lastly, another challenge of this study could be the methodological complexities of the stepped wedge cluster randomized controlled trial design. This is a novel study design that is increasingly being used in the evaluation of service innovations in healthcare organisations [38, 52]. We have chosen this study design because the CDSS-OPTIMED intervention cannot be implemented all at once but must be rolled out sequentially. However, the stepped wedge design has also some methodological complexities, including the possibility of within cluster contamination, and the possibility of time varying treatment effects [38]. Statistical analysis and simple size calculation will account for the confounding effect of time. In addition, the statistical analysis will take into account both the clustered nature as well as the stepped wedge design of the study. In developing this study, we have tried to avoid within-cluster contamination, because participating patients cannot be exposed to both the control group and the intervention group, and we have built transition periods into the design.

## Conclusions

The AMUSE study will examine whether the use of CDSS-OPTIMED, a software program that gives weekly personalized medication recommendations to attending physicians of patients with an estimated life expectancy of three months or less, improves patients’ quality of life. We hypothesize that greater attention to polypharmacy, by using CDSS-OPTIMED, could lead to improved quality of life in patients with a life expectancy of three months or less. In addition, we expect that the intervention will lead to improved medication management. If this study has its hypothesized positive outcome, the results of this study can be used to develop practical guidelines and a standardized method to help physicians with deprescribing medication.

## Data Availability

No datasets were generated or analysed during the current study.

## Abbreviations

CDSS-OPTIMED: Clinical Decision Support System for patients with a life expectancy of less than three months
CONSORT: Consolidated Standards of Reporting Trials
EORTC: European Organization for Research and Treatment of Cancer
PIM: Potentially Inappropriate Medication
QLQ-C15-PAL: Quality of Life Questionnaire Core 15 Palliative Care
QLQ-C30: Quality of Life Questionnaire Core 30
